## Abstract

**Background:**

Substance misuse, including problematic drug and alcohol use, are significant issues in society that can have multiple detrimental effects. Many people access support for their substance misuse during prison sentences, due to the associations between substance misuse and offending, and the high proportion of the prison population who have drug and alcohol issues. Breaking Free Online Health and Justice is a computer-assisted therapy program that has been developed to support substance-involved offenders to address their substance misuse and associated offending within prison settings.

**Methods:**

This will be a parallel-group randomized controlled trial of 4-week Breaking Free Online Health and Justice program as an adjunct to standard treatment for substance misuse, in comparison to standard treatment only, in a male Category D open prison. Interventional and control groups will be compared in terms of the changes in their scores on multiple measures from baseline to post-treatment assessment at 4-weeks, and then 3- and 6-months follow-up. Participants will be adult male offenders serving sentences in prison in England who have demonstrable difficulties with drugs and/or alcohol for at least the past 12-months. The primary outcome measure will be self-reported substance misuse, with secondary outcomes being standardized psychometric assessments of substance dependence, mental health, biopsychosocial functioning, quality of life and post-release offending. Other secondary measures will include frequency of completion of specific intervention strategies in the program.

**Discussion:**

This study will examine whether Breaking Free Online Health and Justice as an adjunct to standard substance misuse interventions in prisons, improves outcomes for substance-involved offenders receiving interventions in custodial settings. Findings from the study will be used to inform further developments of the program and potential improvements to custodial treatment.

**Trials registration:**

ISRCTN09846981.

**Electronic supplementary material:**

The online version of this article (10.1186/s40352-018-0078-1) contains supplementary material, which is available to authorized users.

## Background

Substance misuse, including problematic drug and alcohol use, are significant issues in society that can have multiple detrimental effects. Substance misuse is implicated in a number of criminal offences, including acquisitive crime (Comiskey et al. 2012; Hayhurst et al. 2013), anti-social and violent behavior (Boden et al. 2012; Lundholm et al. 2013), domestic and intimate partner violence (Stuart et al. 2008; Wilson et al. 2017) and child neglect Solis et al. (2012). Links between substance use and criminal behavior are identified within the research literature (Bennett et al. 2008; Hough 2002; Schroeder et al. 2007). Levels of crime reported by substance users during periods of use (Ball et al. 1983; Bennett and Holloway 2009; Bennett et al. 2008; Best et al. 2001; Goldstein 1985; Gossop et al. 2000; Inciardi 1979; McGlothlin et al. 1978), and the high proportion of the prison population who are substance misusers (Budd et al. 2005; Jones et al. 2007; Phillips 2000; Young et al. 2011) all indicate that substance misuse and offending often co-occur and that substance misuse is a primary “criminogenic” factor (Weekes et al. 1999).

In the 2016 Crime Survey for England and Wales, 8.4% of 16–59 year old participants living in the UK reported using an illicit drug within the last 12-months, which, if representative, would extrapolate to approximately 2.7 million people (Home Office 2016). The economic costs to society of substance misuse are substantial, with problematic alcohol misuse alone being estimated to have cost £ 47 billion in 2016 (PHE 2016). Recent data reported by Public Health England from the National Drug Treatment Monitoring System demonstrate that overall, 279,793 adults were in contact with drug and alcohol services between 2016 and 2017 (PHE 2017), with 26% of those receiving treatment for opiate dependence being referred into treatment by criminal justice services. Furthermore, up to 48% of those seeking treatment for both opiate and ‘novel psychoactive substance’ dependence were referred via the criminal justice system (PHE 2017). And additionally, a recent systematic review which included studies from multiple countries, found that both alcohol use disorder and substance use disorder are highly prevalent amongst the prison population, with pooled prevalence estimates of each being 24% and 51% respectively Fazel et al. (2017).

Given the significant associations between substance use and offending, it seems intuitive that if any intervention for substance-involved offenders is to be effective, it needs to address not only the substance use but also the offending behavior that may be associated with it Elison et al. (2017a). In order to meet this requirement, Breaking Free Online (BFO) Health and Justice, a computer-assisted therapy (CAT) program designed to address both substance misuse and offending behaviors simultaneously, has been developed. Such CAT approaches have the potential to widen access to evidence-based treatment for substance misusing individuals as they can be delivered at scale, and because intervention content is delivered via a computer in a highly standardized way, CAT can enhance treatment fidelity and thus treatment effectiveness (Bickel et al. 2008; Moore et al. 2011).

This criminal-justice specific version of BFO has been developed via modification of a version of the program that has been delivered in community-based substance misuse treatment settings for the past eight-years. Published research informed by guidance by the UK Medical Research Council (MRC) around the development and evaluation of complex interventions (Craig et al. 2008; Moore et al. 2015) has examined the evidence-base underpinning the clinical content of BFO (Dugdale et al. 2016b), and barriers and facilitators of the implementation of the program in real-world treatment settings (Dugdale et al. 2017; Dugdale et al. 2016a, b; Elison et al. 2014a, b; Ward et al. 2017). Research examining the effectiveness of the program (Elison et al. 2015a, b; Elison et al. 2014a, b; Elison et al. 2017d) has demonstrated significant reductions in substance dependence and use, and significant improvements in mental health and broader psychosocial functioning. Examination of the mechanisms of action of BFO has demonstrated that users follow tailoring advice provided by the program, that the program exhibits a ‘dose-response’, and that completion of cognitive restructuring strategies in the program underpins changes to broader biopsychosocial functioning (Elison et al. 2017c).

Since 2015 BFO has been available in prisons in addition to community settings via the ‘Virtual Campus’ (VC), the UK prisons IT infrastructure that allows offenders to access a limited range of online programs to support their education, training and employment. However, BFO has become the first *healthcare* program to be included on VC, and the first digital intervention for offenders to be accredited by the UK Ministry of Justice, Correctional Services Advice and Accreditation Panel. Mixed-methods research conducted by the authors explored both the barriers and facilitators of implementation of BFO in prison settings (Elison et al. 2015c; Elison et al. 2016b), and examined clinical outcomes for offenders accessing the program as part of the ‘Gateways’ through-care initiative (Elison et al. 2015c; Davies et al. 2017), which aimed to support substance-involved offenders as they transition back to the community.

Qualitative interview data from 16 offenders engaging with BFO and 10 members of prison staff supporting them suggested that both offenders and staff were able to overcome initial anxieties about using digital technology. Offenders reported the program supported them to develop coping skills to enable them to remain abstinent from using drugs and alcohol, and therefore reduce their chances of reoffending when they were released (Elison et al. 2015c). Staff reported that they felt the program provided an opportunity for offenders to access an evidence-based intervention to allow them to work on their drug and alcohol difficulties, and also provided an opportunity to use the VC in a novel way to further support offender rehabilitation (Davies et al. 2017). Analyses of quantitative clinical outcomes from a sample of 151 male offenders accessing BFO before being released from prison (Davies et al. 2017; Elison et al., 2015c), demonstrated significant reductions in alcohol and drug dependence and consumption, significant improvements in quality of life, and significant improvements in multiple aspects of broader biopsychosocial functioning. However, only within-subject analyses were conducted in this research, with no ‘standard treatment’ control group having been included in the research conducted to date.

## Method

### Aims

This study will evaluate, via a randomized controlled trial (RCT) methodology, the efficacy of BFO as a supplement to standard treatment, within a criminal justice setting. The principle aim of this study is therefore to determine the effectiveness of BFO delivered alongside standard treatment, in comparison to standard treatment only, in reducing alcohol and drug consumption and dependence, and any possible impact on mental health and broader biopsychosocial functioning. It is anticipated that delivery of BFO alongside standard treatment should confer some added benefits to participants engaging with this novel intervention, when compared to participants engaging with standard treatment only. This means there may be some post-treatment differences between the two study groups in terms of substance-related outcomes and broader biopsychosocial functioning.

### Design

This will be a randomized, parallel-group longitudinal comparison study of 4-week periods of either i) BFO plus standard treatment, or ii) standard treatment only, using intention to treat (ITT) analyses to examine outcomes.

### Setting

The study will be conducted in an adult male prison in North-West England, UK, where the BFO program is not currently delivered as a standard treatment. This prison is a ‘Category D’ open prison where offenders are, subject to approval, provided with ‘Release on Temporary License’ (ROTL) where they are granted release to work in the community or have ‘home leave’. This prison is a resettlement prison which has an operational capacity of just over 600 male offenders, approximately a quarter of whom are either on life sentences or subject to indeterminate sentences. Approximately, 75% of the men in the prison are serving sentences of 4-years or longer at any one time. Around three-quarters of the men in the prison are over the age of 30 years, and around 40% have identified substance misuse difficulties. The prison places a strong emphasis on rehabilitation and community reintegration, running a range of vocational training courses, alongside initiatives to support the men serving sentences in the prison to maintain and enhance the relationships they have with their families.

This category of prison has been chosen for the study because, although even the very highest security prisons in the UK have significant issues with drug and alcohol use, offenders in a Category D prison may potentially have the most opportunity to use substances, as they spend some of their time in the community. Most participants may be on ROTL during the study, including resettlement day release, and resettlement overnight release, so it is more likely that outcomes related to substance use will be an artifact of treatment effects, rather than lack of opportunity to use substances due to incarceration in a highly secure environment. Although it is anticipated that most, if not all, participants will be receiving ROTL during the study, the ROTL status of each participant will be recorded during their first treatment session and this will be taken into account during data analyses, if there are a significant number of participants not provided with ROTL during the study. Participants will be recruited from standard alcohol and drug misuse services in the prison, which are delivered in coordination with Her Majesty’s Prison and Probation Service (HMPPS).

### Participants

Participants included in the study will be offenders currently serving a prison sentence aged 18 to 65 years with problem alcohol and/or drug use of duration of 12-months or longer. This period of time is in line with DSM-V criteria for substance related disorders (American Psychiatric Association 2000). It is estimated that a total of 240 participants will need to be recruited and screened in order to obtain a sample of 120 evaluable participants (see ‘Power Calculation’).Inclusion criteriaMale offenders currently serving a prison sentence with problem alcohol and/or drug use aged 18 to 65 years.Willing and able to give informed consent for participation in the study.Has at least 3-months left to serve of their sentence at the prison acting as the research site, at the time they are recruited to the study.Problem alcohol and/or drug use present for at least 12-months prior to current prison sentence.Willing to follow treatment for problem alcohol and/or drug use for 4-weeks.Willing to provide outcome measures at 3- and 6-months follow-up.Concomitant alcohol and drug/s use permitted, as well as any prescribed medication.Exclusion CriteriaParticipation in any other alcohol and/or drug related clinical studies.Individuals detained under the Mental Health Act.Individuals with a known and diagnosed intellectual or developmental disability.Non-English speaking offenders (study information material and program only produced in English).

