The Informed Consent Form will be signed and dated by both the participant and the site investigator, and the participant’s preferred mode of contact (e.g. telephone, email etc.) and contact details for the completion of follow-up assessments will also be noted at this point. The participant will be provided with a copy of the signed consent form and the Participant Information Sheet. The original consent forms will be retained in a secure storage facility separately from source data to protect against breach of privacy and participant anonymity.

If written consent is given, each participant will then be screened for eligibility by the site investigator before then being randomized to either the BFO or control group. Randomization will occur at the level of the individual participants, with participants being assigned to one of the study groups following the generation of a random allocation sequence via the *Research Randomizer* (from the Social Psychology Network- Urbaniak and Plous 2011). Sequentially-numbered opaque sealed envelopes containing the treatment group that the participant will be allocated to will be delivered to the research site prior to commencement of the study. The participant number will be determined according to the order of enrolment in the study. The site investigator will assign and open one sealed envelope per participant. A screening log, including the participant number and treatment group assigned by randomization and any subsequent reason/s for exclusion from the study (if applicable), will then be completed by the site investigator.

No longer than 2-weeks after being randomized and completing the eligibility screening, both study groups will complete a battery of assessments to collect data around primary and secondary outcomes and demographic information including age and ethnicity. This battery of assessment will be delivered digitally via desktop computers within the prison IT suites. The assessment for the BFO group will be completed within the BFO program. The control group will complete the measures via a specially developed digital assessment platform which will deliver the same assessment that is included in the BFO program, but without providing access to any of the digital intervention content provided by BFO.

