Follow-up assessments will then also be completed at 3- and 6-months post-treatment with all participants. Follow-up assessments may be completed either in the community if offenders have been released, or in prison if they are still serving their sentence. The site investigators will work with the practitioners delivering both BFO and standard treatments to determine which participants have been released back to the community since completing their 4-week treatment period, and which participants are still serving their sentence in the participating prison. Additionally, those participants who have been transferred to a different prison will also be identified.

Depending on participants’ preference, the site investigators will contact all participants who have been released back to the community via telephone or email, and their assessment will be completed either over the phone, or via a link to an online version of the assessment. The preferred contact details for each participant that were collected at the time of consent and randomization will be used. For those participants who are still serving a prison sentence, or have been reconvicted and are serving a new sentence, or have been transferred to a different prison, they will be visited by the site investigator at their current prison and their follow-up assessment will be completed there.

By following the procedure described above, each participant will take part in the study for a total of approximately 7-months, including 4-weeks of treatment and 3- and 6-month follow-up assessments. It is likely that the study will run for a total of approximately 18-months, which will include enough time for recruitment, running enough successive 4-week long BFO groups to achieve the required sample size, and completion of all 3- and 6-month follow-up assessments.

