### Measures

The primary outcome will be self-reported substance use which will be calculated using answers to two questions i) ‘on a typical day, how many (unit of measurement) of (substance) are you using?’, and ii) ‘in a typical week, how many days are you using (substance)?’. Given the research setting, i.e. a Category D ‘open prison’ where offenders spend time in the community each week, it is more likely that any substance use outcomes will be due to genuine treatment effects, than they would be in a more highly secure prison setting with fewer opportunities to access and use substances. Information about weekly substance use before each participants’ current prison sentence will also be collected.

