There may also be a limitation inherent due to the choice to include an open prison in the study. Open prisons generally contain low-risk offenders who may have already demonstrated that they have made good progress in their rehabilitation. Therefore, a ‘floor effect’ may occur that could artificially under-estimate the effectiveness of the BFO program if participants largely start at a baseline level of relatively good biopsychosocial functioning. Finally, a significant limitation may lie with the possible attrition rates that may be expected from a study that includes substance-involved offenders as participants, as it can be particularly difficult to maintain engagement with individuals who may have issues around substance misuse and offending. Although measures can be put in place to enhance retention of participants whilst they are still serving their prison sentence, such as weekly key-working sessions with practitioners as part of standard treatment, it may be particularly challenging to retain participants in the study once they are released back to the community. Every attempt will be made to contact participants and obtain follow-up data, and it is hoped that as most participants will be in contact with probation services, this may provide a means of contacting participants as they complete their sentences in the community.

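### The 3- and 6-month follow-ups mix released and imprisoned men by design, and time to expected release, obtainable before allocation, is not among the adjustments the article names

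*Protocol article*

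**What the plan says.** All references are to the Protocol article.

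- **Eligibility (Participants).** The requirement is "Has at least 3-months left to serve of their sentence at the prison acting as the research site, at the time they are recruited to" the study. There is a minimum and no maximum.
- **Order of events (Procedure).** After consent, "each participant will then be screened for eligibility by the site investigator before then being randomized". The baseline battery then comes "No longer than 2-weeks after being randomized and completing the eligibility screening", followed by 4 weeks of treatment. Follow-up is at 3 and 6 months, counted from the end of treatment.
- **Place and mode of follow-up (Procedure).** "Follow-up assessments may be completed either in the community if offenders have been released, or in prison if they are still serving their sentence". Released men are assessed by telephone or online link. Men in custody, including those transferred or reconvicted, are visited by the site investigator.
- **Population (Setting).** The prison holds just over 600 men, "approximately a quarter of whom are either on life sentences or subject to indeterminate sentences".
- **Retention (Discussion).** The article accepts that "it may be particularly challenging to retain participants in the study once they are released back to the community".
- **Allocation and adjustment.** Procedure describes a random allocation sequence in sealed envelopes and names no stratification factor. Data analysis names baseline scores as what is controlled for. Setting adds ROTL status, recorded at the first treatment session and used only if a significant number of men lack it.

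**The concern.** The eligibility minimum runs from recruitment, while the follow-up clock starts only when treatment ends. A man who enters with 3 to 4 months left can be out before his first follow-up; a man on an indeterminate sentence may still be inside at his last. Three things then differ between them at the same visit: how freely they can obtain substances, how the self-report is taken, and how likely they are to be reached at all. The first two bear on the primary outcome, which is self-reported use, and the third on who contributes data.

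Time to expected release is a natural pre-randomization predictor of all three, and eligibility screening already looks at remaining sentence before the envelope is opened. The named adjustments do not stand in for it. A baseline use score taken in custody says little about when a man leaves, and ROTL status describes access while he is still serving. At stake is the precision of the 3- and 6-month comparisons and the credibility of any missing-data assumption in a trial that allows for 50% attrition at those visits.

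**Working it through.** **1. Timeline.** Inputs from Procedure: lag from randomization to baseline 0 to 14 days; treatment 28 days; visits 3 and 6 months after treatment. One month = 365.25/12 = 30.44 days, so 28 days = 0.92 months and 14 days = 0.46 months. I take recruitment and randomization as the same day, with treatment starting straight after baseline; any further delay pushes the visits later.

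The article's own figure first: total participation = 0.92 + 6 = 6.92 months without lag, matching its approximately 7 months. This confirms that the visits count from the end of treatment.

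- 4-week assessment: 28 to 42 days, or 0.92 to 1.38 months. This is inside the 3-month minimum, with 7 to 9 weeks to spare.
- 3-month visit: 3 + 0.92 = 3.92, to 3 + 0.92 + 0.46 = 4.38 months. This is past the minimum by 4 to 6 weeks.
- 6-month visit: 6.92 to 7.38 months. This is past the minimum by 17 to 19 weeks.

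**2. Chance imbalance in the share released.** The article does not give the share released by either visit, and its sentence-length figures describe the whole prison rather than the men recruited. I therefore assume p = 10% to 50%; 50% gives the largest variance. With n per arm and unstratified allocation, SE = sqrt(2p(1 − p)/n), the 95% range is ±1.96 × SE, and the chance of a gap of 10 points or more is 2[1 − Φ(0.10/SE)]. The last column multiplies the edge of the range by an assumed release effect of 0.5 SD.

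The Power calculation section gives 60 evaluable per arm. Applying its 50% attrition to those 60 gives 30; reading it as 240 reduced to 120 leaves 60. Both are shown.

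| n per arm | p | SE | 95% range | P(gap ≥ 0.10) | Shift (SD) |
|---|---|---|---|---|---|
| 60 | 0.10 | 0.055 | ±0.107 | 0.07 | 0.05 |
| 60 | 0.25 | 0.079 | ±0.155 | 0.21 | 0.08 |
| 60 | 0.50 | 0.091 | ±0.179 | 0.27 | 0.09 |
| 30 | 0.10 | 0.077 | ±0.152 | 0.20 | 0.08 |
| 30 | 0.25 | 0.112 | ±0.219 | 0.37 | 0.11 |
| 30 | 0.50 | 0.129 | ±0.253 | 0.44 | 0.13 |

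For scale, 60 per arm at two-sided 0.05 and 80% power detects (1.96 + 0.84) × sqrt(2/60) ≈ 0.51 SD. The article states no effect size, so this is a yardstick only.

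**3. Precision.** If release shifts the outcome by g SD, location adds variance v = p(1 − p)g², and ignoring it inflates the required sample by the factor 1 + v. For g = 0.3 and p = 0.25, v = 0.1875 × 0.09 = 0.017. For g = 0.8 and p = 0.50, v = 0.25 × 0.64 = 0.16. The loss is thus equivalent to about 2% to 16% of the sample. This is an upper bound on what a covariate could recover, because expected release predicts location imperfectly.

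**The case against.** **Mixed follow-up is intended.** The criterion never promises custody through follow-up. Assessment in either place is planned openly, post-release offending is a secondary outcome that requires some men to be released, and the retention risk is disclosed. This stands: a reader might infer a contradiction or a feasibility error, and there is none.

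**Randomization already protects the comparison.** Remaining sentence is balanced in expectation, and chance imbalance is reflected in the standard errors. This also stands. A reader might infer a systematic bias for or against the program; the design does not produce one by this route. The 4-week comparison is unaffected.

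**The opportunity argument.** A reader might infer that release defeats the reasoning in Setting and Measures, where "it is more likely that any substance use outcomes will be due to genuine treatment effects". That does not follow. Both passages compare the open prison with a highly secure one. Release increases opportunity, so it does not bring back lack of opportunity as an explanation, and the argument need not be confined to the 4-week assessment.

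**The analysis plan is not shown.** It may list further covariates, and a condensed article may leave out stratification. This limits the point to what the article names. It does name its adjustments, and time to release is not one of them.

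**Stratifying would achieve little.** Two envelope series balance nothing unless each is blocked, and a single cut near the last visit does not separate released from imprisoned men at the 3-month visit. This stands, so the remedy is a covariate. Nor is it quite free of data collection: the criterion itself needs only a yes or no at 3 months.

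**Conclusion.** The point holds as a low-cost improvement to the 3- and 6-month analyses. The eligibility minimum expires 4 to 6 weeks before the first follow-up and 17 to 19 weeks before the second. Those visits therefore combine men in different circumstances, and the article names no adjustment for a pre-randomization variable that plausibly predicts both the outcome and its absence.

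The size is modest: a shift of about 0.05 to 0.09 SD at 60 per arm or 0.08 to 0.13 SD at 30 per arm, at the edge of chance imbalance, plus some lost precision. These figures rest on an assumed released share of 10% to 50% and an assumed release effect of 0.5 SD, neither of which the article supplies. The gain for missing data is not quantified: if released men are lost more often, conditioning on expected release makes a missing-at-random assumption more credible than conditioning on baseline scores alone.

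**What to change.** When the sentence criterion is checked, and before the envelope is opened, record months to earliest expected release, or indeterminate. Prespecify this value as a covariate in the between-arm models at 3 and 6 months, for example in three categories split at about 4.5 and 7.5 months (the latest timing of the two visits, rounded up), with indeterminate sentences in the last. Use the same variable in any missing-data model. The 4-week model does not need it.

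Do not adjust for actual release status at the visit: it arises after randomization and could be affected by treatment. Stratified allocation is optional and helps only if each envelope series is blocked; if the envelopes already exist, the covariate is enough.

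The cost is one recorded value per man and one or two degrees of freedom in the follow-up models. No extra participants or visits are needed.
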